# Effectiveness of a multi-faceted intervention to deprescribe proton pump inhibitors in primary care: protocol for a population-based, pragmatic, cluster-randomized controlled trial

**DOI:** 10.1186/s12913-022-07496-3

**Published:** 2022-02-17

**Keywords:** Deprescriptions, Proton pump inhibitors, Patient outcome assessment, Primary care, Cluster analysis, Multi-faceted intervention

## Abstract

**Background:**

Inappropriately using proton pump inhibitors (PPI) is associated with severe adverse drug reactions and may have major consequences on healthcare costs. Deprescribing (the process by which a healthcare professional supervises the withdrawal of an inappropriate medication, to manage polypharmacy and improve outcomes) should be considered when an inappropriate PPI prescription is identified. Deprescribing interventions directed solely to prescribers have limited efficacy and are rarely targeted to patients. The aim of this trial is to assess the efficacy of a multi-faceted intervention with patients and general practitioners (GPs) to deprescribe PPI.

**Methods:**

We will conduct a pragmatic***,*** cluster-randomized, population-based, controlled trial in two regions of Western France. GPs with practices with over 100 patients, and their adult patient to whom over 300 defined daily doses (DDD) of PPIs have been dispensed in the year before baseline will be included. A total of 1300 GPs and 33,000 patients will be cluster-randomized by GPs practices. Three arms will be compared: i) a multi-faceted intervention associating a) a patient education brochure about PPI deprescribing sent directly to patients (the brochure was designed using a mixed-methods study), and b) a personalized letter with the Bruyere’s PPI deprescribing algorithm sent to their respective GPs, or ii) a single intervention where only the GPs received the letter and algorithm, or iii) no intervention.

The primary outcome will be PPI deprescribing, defined as the proportion of patients achieving at least a 50% decrease in the amount of PPI dispensed to them (DDD/year) at 12 months compared to baseline. Secondary outcomes will include incremental cost-utility ratio (using EQ-5D-5L scale and National Health Insurance’s database), acid rebound (using the Gastroesophageal Reflux Disease Impact Scale), and the patients’ attitudes towards deprescribing (using the French rPATD).

**Discussion:**

Based on previous trials, we anticipate more than 10% “successful PPI deprescribing” in the multi-faceted intervention compared to the single intervention on GPs and the control arm*.* The study has been funded through a national grant and will be launched in autumn 2020, for early results by the end of 2022.

**Trial registration:**

Clinicaltrials.gov NCT04255823; first registered on February 5, 2020.

**Supplementary Information:**

The online version contains supplementary material available at 10.1186/s12913-022-07496-3.

## Background

Proton pump inhibitors (PPI) are frequently prescribed inappropriately for excessive durations or inadequate indications in Europe [1, 2], the United-States [3] and France [4]. This inappropriate PPI use is associated with an increased risk of renal adverse events (acute interstitial nephritis, chronic renal failure) [5], *Clostridium difficile* diarrhea [6], pneumonia [7], fractures [8], dementia [9] or cardiovascular events [10]. Also, more recently, two studies discussed an associated, increased risk of colorectal cancer [11] and even mortality [12] with long-term PPI use compared to histamine-2 receptor antagonists. Additionally, excessive PPI use may have major consequences on healthcare costs. PPI reimbursements represented a total cost of $12 billion in the United-States, in 2015 [13] and £87 million in England, in 2018 [14], and is expected to rise since PPI prescriptions are continuously increasing [15].

Deprescribing is defined as “the process of withdrawal of an inappropriate medication, supervised by a healthcare professional with the goal of managing the polypharmacy and improving outcomes” [16]. Although some interventions have been developed to promote deprescribing of PPIs among physicians, pharmacist or nurses, they have limited efficacy [17]. However, multi-faceted interventions that include patients have demonstrated greater success in Australia, the United-States, and Europe [18–20].

### Trial objectives

The primary objective of this study is to assess if a multi-faceted intervention is superior to single intervention and usual care to increase PPI deprescribing. Three arms will be compared: i) a multi-faceted intervention with patients using a patient education brochure and with their general practitioners (GPs) using both a personalized letter and a deprescribing algorithm ii) a single intervention on GPs and iii) no intervention (usual care).

Secondary objectives are to assess if the multi-faceted intervention has an economic efficiency compared to control group by performing a cost-utility analysis, to determine the gastroesophageal reflux disease (GERD) symptom recurrence rate, the patients’ attitudes toward deprescribing, and the characteristics of patients engaging in the deprescribing process.

### Study hypothesis

We hypothesize that each of the deprescribing interventions will increase PPI deprescribing rates compared to usual care, and that the multi-faceted intervention (directed to both GPs and patients) will be superior.

## Methods

### Study design and setting

The trial is designed as a prospective, open-label, cluster-randomized parallel-controlled study within a 12-month period. The unit of randomization will be the GPs practice. This pragmatic population-based trial will be conducted in every eligible GP practice in two regions of Western France (Loire-Atlantique and Vendée).

### Study population

We will include both patients and their regular GPs if the GP has a regular patient population of more than 100 patients per year. Eligible patients must be affiliated to the French health national insurance system (Caisse Primaire d’Assurance Maladie, CPAM), and have been dispensed more than 300 defined daily doses (DDD) of PPI in the 12 months before baseline, estimated using the local health insurance reimbursement database (SIAM-ERASME). Those patients at risk of gastroduodenal lesions i.e. treated with nonsteroidal anti-inflammatory drugs (NSAIDs) and over 65 years old or treated with either corticosteroids or anticoagulants or platelet aggregation inhibitors will be excluded.

### Recruitment and allocation

Each GP practice and its associated patients will be defined as an individual cluster to avoid contamination bias between GPs and/or between patients [21]. These clusters will be randomized in three arms using a 1:1:1 ratio. Eligible patients will be identified using the local health insurance reimbursement database.

### Blinding

Blinding of patients and GPs will not be feasible given the pragmatic nature of the intervention. However, the research team will be blinded to the intervention designated to each arm.

### Interventions

Two interventional arms and a control arm are planned (Fig. 1). The multi-faceted PPI deprescribing intervention will combine sending information to both patients and GPs. Patients will receive an education brochure and GPs will receive a personalized letter and deprescribing algorithm. The single PPI deprescribing intervention for GPs will consist of a personalized letter and deprescribing algorithm. The control arm will receive no deprescribing educational materials (usual care).

**Fig. 1 Fig1:**
[figure not shown]
Study design

The selected deprescribing algorithm is an evidence-based clinical practice guideline [22] with the highest AGREE II score (unpublished data) [23], which was translated into French (supplementary material 1). We developed the patient education brochure using a previously reported mixed-method study [24] (supplementary material 2).

### Outcome measures

#### Primary outcome

PPI deprescribing will be defined as the proportion of patients achieving a 50% decrease in their PPI reimbursement (Defined Daily Dose (DDD)/year) at the end of the intervention (at 12 months compared to baseline).

#### Secondary outcomes

Incremental cost-utility ratios: cost by quality-adjusted life-years (QALY) ratios comparing the intervention groups to control group. QALYs will be assessed from patient responses to the EuroQoL EQ-5D-5L questionnaire [25].GERD symptom recurrence using the GERD Impact Scale questionnaire [26].Patient attitude towards deprescribing using the French version of the Revised Patient Attitudes Toward Deprescribing (rPATD) [27], the *Attitude des patients envers la déprescription* (APaD) [28].Patient characteristics that succeed in deprescribing PPIs using data collected from health insurance reimbursement database.

### Data collection procedures

Baseline patient variables (age, sex, PPI reimbursement, chronic disease, free complementary health insurance for economically vulnerable patients) and GP variables (age, sex, activity type and city classification) will be collected using the local health insurance reimbursement database (SIAM-ERASME) (Fig. 2).

**Fig. 2 Fig2:**
[figure not shown]
First collection from local health insurance database 1 month before baseline and data flow. ^1^PPI DDD/year: Proton pump inhibitors defined daily dose per year; ^2^GPs: General practitioners

Healthcare resource consumption over a one-year period will be collected by combining PPI use and medical expenses related to ambulatory care (histamine-2 receptor antagonists and antacids reimbursements, consultations, technical procedures and laboratory tests). These data will be collected using the local health insurance reimbursement database (SIAM-ERASME) 12 months after baseline.

Hospital service use will be collected using the French National Health Data System (*Système National des Données de Santé*, SNDS) [29].

Measuring health-related quality of life, GERD recurrence and attitudes toward deprescribing, requires sending self-administered questionnaires with pre-paid return envelopes and to scheduling phone calls to minimize missing answers. Thus, the analysis will only be performed on a 10% sample of the population.

Thus, the EQ-5D-5L, GERD Impact Scale and rPATD questionnaires will be mailed to a 10% patient sample in each arm, 1 month before and 12 months after baseline. Patients will return the three self-reported questionnaires to the National Health Insurance by post. Phone calls will be scheduled between 8 and 10 days later to remind patients to return the three questionnaires.

The Health Insurance data managers will pair the data collected from these databases at the patient level, and proceed to data anonymization before transmission to the statistician (Fig. 3).

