#### Secondary analyses

##### Cost-utility analysis

The cost-utility analysis will aim to estimate incremental cost-utility ratios (ICUR) of cost per QALY comparing the multi-faceted intervention arm and single intervention on GP arm to control arm (usual care) as follows:

ICUR = [costs _deprescribing arm_ - costs _usual care arm_] / [QALYs _deprescribing arm_ - QALYs _usual care arm_].

The costs over a one-year time horizon will be estimated from a societal perspective excluding indirect costs such as production losses as recommended by French National Guidelines on the economic evaluation of health care programs [31]. To estimate costs, the healthcare resources consumed including, PPI consumption, medical consultations, examinations, laboratory analyses and hospitalization will be valued in monetary terms using conventional tariffs of the French National Health Insurance System.

Quality of life obtained will be measured with QALYS. QALYs are a numerical composite index combining information about quality of life and survival. They are constructed by weighting each year by a quality of life factor - called a utility score - typically ranging from 0 (death) to 1 (perfect health) such that a higher score represents a more preferred health state. They will be estimated from the patient answers to the EQ-5D-5L questionnaires sent at baseline and at 1 year. The EQ-5D-5L is a generic health status questionnaire that has five dimensions (mobility, self-care, usual activities, pain/discomfort, and anxiety/depression) each of which has five levels denoting increasing problems with the dimension under consideration. The patients answers will be converted to utility scores using the French published tariffs for the EQ-5D-5L [32]. Given the time horizon of 1 year, QALYs and costs will not be discounted.

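### Apart from PPI reimbursement, no pre-baseline resource use is listed, so the incremental cost cannot be adjusted for total prior-year cost

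*Protocol article*

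**What the plan says.** All references are to the protocol article.

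- **Baseline extraction** (Data collection procedures): "Baseline patient variables (age, sex, PPI reimbursement, chronic disease, free complementary health insurance for economically vulnerable patients". PPI reimbursement is the only expense item among these. The same database is already read back over the year before baseline for eligibility, since patients must "have been dispensed more than 300 defined daily doses (DDD) of PPI in the 12 months before baseline" (Study population).
- **Ambulatory costs** (same section, after the Fig. 2 legend): "Healthcare resource consumption over a one-year period will be collected by combining PPI use and medical expenses related to ambulatory care". The items are H2 antagonists and antacids, consultations, technical procedures and laboratory tests. On timing: "These data will be collected using the local health insurance reimbursement database (SIAM-ERASME) 12 months after baseline".
- **Hospital costs** (same place): "Hospital service use will be collected using the French National Health Data System". No time window is given.
- **Cost-utility analysis**: "The costs over a one-year time horizon will be estimated from a societal perspective excluding indirect costs". The components are "the healthcare resources consumed including, PPI consumption, medical consultations, examinations, laboratory analyses and hospitalization". Incremental costs and QALYs are to be estimated by seemingly unrelated regression, with multiple imputation for missing data. Neither the covariates nor the imputation predictors of this analysis are named.
- **Other outcomes**: PPI dispensing has a pre-baseline value from the database, and the EQ-5D-5L, GERD Impact Scale and rPATD are mailed one month before baseline.

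**The concern.** Total cost is the numerator of the cost-utility ratio. It is the one compared quantity for which only part of the pre-intervention value, the PPI part, is listed. Costs that include hospital stays are usually skewed and driven by a minority of patients. The article describes no cost distribution, so that is a general expectation and not something taken from the document. A patient's own spending in the previous year is a natural candidate to explain some of that variation.

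At stake is how wide the interval around the incremental cost will be, and how far a chance excess of high-cost patients in one arm can move the incremental cost, the ratio and the acceptability curves. QALYs rest on questionnaires sent to a 10% sample of nearly 3300 patients (Limitations), about 1100 per arm before non-response, so precision is limited there too.

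The point concerns extraction more than modelling. An analysis plan can choose covariates, but only from variables that were extracted. The article says that data managers pair the databases at patient level and anonymise them before the statistician receives them, so a variable left out at that step may be hard to add later.

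**Working it through.** **No stated figure to reproduce.** The article gives no standard deviation, intracluster correlation, between-year correlation or precision for cost. The calculation below shows only what the missing covariate could be worth.

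**Inputs from the article:** 33,000 patients, 684 practices, 48.3 patients per practice (Sample size and power); 1:1:1 allocation of practices (Recruitment and allocation), hence 684/3 = 228 practices and about 11,000 patients per arm; 10% questionnaire sample, about 1100 per arm and 4.83 per practice.

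**Assumed inputs:** correlation ρ between prior-year and study-year total cost of 0.3 to 0.7; cost intracluster correlation of 0.05, borrowed from the value stated for deprescribing.

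**Step 1: gain against no adjustment.** Linear adjustment for a baseline covariate multiplies the variance of the arm difference by 1 − ρ², the standard error by √(1 − ρ²), and is worth 1/(1 − ρ²) times the sample.

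| ρ | Variance reduction | SE multiplier | Equivalent sample |
|---|---|---|---|
| 0.3 | 9% | 0.954 | 1.10 |
| 0.5 | 25% | 0.866 | 1.33 |
| 0.7 | 49% | 0.714 | 1.96 |

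**Step 2: what that means for the interval.** In units of the cost SD, SE = √(2·DE/n) with DE = 1 + (m − 1)·ICC.

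- 10% sample: DE = 1 + 3.83 × 0.05 = 1.19; SE = √(2 × 1.19/1100) = 0.0465; 95% half-width 1.96 × 0.0465 = 0.091 SD. With adjustment at ρ = 0.3, 0.5 and 0.7 it becomes 0.087, 0.079 and 0.065 SD.
- All patients, if costs are analysed in everyone: DE = 1 + 47.3 × 0.05 = 3.365; SE = √(2 × 3.365/11,000) = 0.0247; half-width 0.0485 SD, becoming 0.046, 0.042 and 0.035 SD.

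The proportional gain is the same in both cases. Step 2 assumes that ρ applies equally within and between practices.

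**Step 3: gain beyond a variable already collected.** Suppose baseline PPI reimbursement alone has correlation ρ₀ with study-year cost, and full prior-year cost, which contains it, has ρ₁ = 0.5. The further SE reduction is 1 − √[(1 − ρ₁²)/(1 − ρ₀²)]:

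- ρ₀ = 0.1: 1 − √(0.75/0.99) = 0.13
- ρ₀ = 0.3: 1 − √(0.75/0.91) = 0.09

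The further reduction is thus about 9% to 13%. Age, chronic disease and insurance status, also collected, would take up some of this as well.

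**The case against.** The strongest reply is that nothing here is stated wrongly. A one-year horizon and one year of resource use agree with each other. Practices are randomised, about 228 per arm, so a comparison of follow-up costs is unbiased in expectation. Chance imbalance is ordinary sampling error, which the acceptability curves are meant to display. A condensed article need not list every covariate, and the two figures that show the extractions are not available in the text read here. All of this stands, and it limits the point to an improvement in efficiency. It does not remove the point, because the article does list its baseline variables and does date its ambulatory cost extraction, and non-PPI ambulatory costs before baseline appear in neither.

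A reader might infer more than the article supports:

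- *That no pre-baseline cost is collected.* PPI reimbursement is a baseline variable and PPI consumption is a cost component.
- *That hospital costs are confined to the follow-up year.* The SNDS window is not stated. Nor would the local database supply hospital use, which comes from the SNDS.
- *That the incremental cost is biased.* Randomisation rules this out as an expectation.
- *That the gain equals up to 96% more patients for the cost-utility result.* That figure takes the top of an assumed range, compares with no adjustment at all, and concerns cost only. The ratio and net benefit also carry QALY variance, which this covariate need not reduce. Costs dominated by rare admissions may also correlate weakly between years.
- *That costs will be analysed only in about 3300 patients.* The article restricts the questionnaire outcomes to the 10% sample and is not explicit about the database costs.

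**Conclusion.** The point holds as a cheap improvement to a secondary analysis; it is not an error. As described, the incremental cost can be adjusted for prior PPI reimbursement, age, sex, chronic disease and insurance status, but not for total prior-year cost. The loss is in precision and in protection from chance imbalance. Under an assumed between-year correlation of 0.3 to 0.7, the variance reduction forgone is 9% to 49% against an unadjusted analysis, and less against an analysis that uses what is already collected. The range rests entirely on that correlation, which the article does not give. The conclusion also assumes that the unseen figures and any fuller protocol do not already list prior-year costs.

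**What to change.** 1. In Data collection procedures, add to the baseline variables the reimbursed ambulatory cost for the 12 months before baseline, in the same categories as the follow-up extraction from SIAM-ERASME.
2. State the window of the SNDS hospital data and, where feasible, extend it to the same 12 months.
3. Do both before the databases are paired and anonymised. Trial status describes SNDS collection as running until the end of 2022, so that request may still be open. If the SIAM-ERASME data, planned for mid-November 2021, have already been paired and anonymised, the data managers would have to say whether prior-year costs can still be added.
4. In Cost-utility analysis, name prior-year cost as a covariate in the cost equation of the seemingly unrelated regression and as a predictor in the multiple imputation.

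The cost is a wider date range in two data requests and modest data-management work. No patient contact or recruitment is involved. If only the SIAM-ERASME part is feasible, ambulatory prior cost alone can still be used, with a smaller gain than full prior cost would give.

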**Fig. 3 Fig3:**
[figure not shown]
Second data collection from local health insurance database 12 months after baseline and data flow. ^1^GPs: General practitioners; ^2^SNDS: French national Health data System (*Système National des Données de Santé*)

### Sample size and power

Preliminary analyses showed that around 33,000 patients, 1300 GPs and 684 practices would meet inclusion criteria in 2017, which corresponds to a mean of 1.9 GPs and 48.3 patients per practice. Using an intraclass correlation coefficient (ICC) of 0.05 thus lead to an inflation factor of 3.365. Literature data suggested a “natural” PPI deprescribing rate between 2 and 7% in the control arm [17, 20, 30].

Assuming an inflation factor of 3.365 and using a two- sided alpha of 0.05, we will have 90% power to detect a minimum true difference of 9.5% of PPI deprescribing rates between the multi-faceted intervention arm and the control arm. These estimates change slightly if different natural deprescribing rates and higher ICCs are assumed (Table 1).

**Table 1 Tab1:** Sample size simulation

“Natural” PPI deprescribing rate	PPI deprescribing rate due to intervention	Patients per cluster	Intracluster Correlation Coefficient	Power
2%	17%	45	0.05	> 0.999
2%	17%	50	0.05	> 0.999
2%	17%	45	0.1	> 0.999
2%	17%	50	0.1	> 0.999
2%	10%	45	0.05	> 0.999
2%	10%	50	0.05	> 0.999
2%	10%	45	0.1	> 0.999
2%	10%	50	0.1	> 0.999
7%	17%	45	0.05	> 0.999
7%	17%	50	0.05	> 0.999
7%	17%	45	0.1	> 0.999
7%	17%	50	0.1	> 0.999
7%	10%	45	0.05	> 0.994
7%	10%	50	0.05	> 0.990
7%	10%	45	0.1	> 0.930
7%	10%	50	0.1	> 0.908

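### The inflation factor 3.365 and the Table 1 powers assume practices of equal size, so the 7% versus 10% entries are best-case values wrongly shown as lower bounds (minor)

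*Protocol article*

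**What the plan says.** All the inputs are in the protocol article.

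- **Sample size and power.** The 2017 extract found that "around 33,000 patients, 1300 GPs and 684 practices would meet inclusion criteria in 2017", which the article summarises as "a mean of 1.9 GPs and 48.3 patients per practice". It continues: "Using an intraclass correlation coefficient (ICC) of 0.05 thus lead to an inflation factor of 3.365". The test level is given as "using a two- sided alpha of 0.05". On the control rate: "Literature data suggested a “natural” PPI deprescribing rate between 2 and 7% in the control arm".
- **Table 1.** Cluster size appears only as one fixed value, 45 or 50. For 7% versus 10% the printed powers are > 0.994 (45 patients, ICC 0.05), > 0.990 (50, 0.05), > 0.930 (45, 0.1) and > 0.908 (50, 0.1). The other twelve rows all read > 0.999.
- **Recruitment and allocation.** "Each GP practice and its associated patients will be defined as an individual cluster", and "These clusters will be randomized in three arms using a 1:1:1 ratio".
- **Study design and setting.** The trial is "conducted in every eligible GP practice in two regions of Western France".
- **Primary analysis.** A generalized linear mixed model with a random effect for practice.

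The section gives no standard deviation, range or CV of practice size, and no allowance for unequal sizes.

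**The concern.** The usual design effect, 1 + (m − 1) × ICC, is exact only when every cluster has m patients. When sizes vary around the same mean, the same total number of patients carries less information and power falls.

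Nothing in this design holds practice size constant. Practices enter whole, there is no cap, and the eligibility rule on the GP's patient list sets only a minimum. A mean of 1.9 GPs is not a whole number, so practices cannot all have the same number of GPs. The least variable split that gives this mean is 10% of practices with one GP and 90% with two. Its variance is 0.1 × 0.9² + 0.9 × 0.1² = 0.09, so the CV is 0.3/1.9 = 0.16 from GP numbers alone. Differences between GPs in their number of eligible patients would normally add to this.

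What is at stake is the accuracy of four printed powers. They are the only rows of Table 1 that do not read > 0.999, so they are the only ones that show how small a difference the trial can reliably detect.

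**Working it through.** **Inputs.** 33,000 patients in three equal arms give 11,000 per arm. Mean practice size is 48.3 (Table 1 uses 45 and 50). ICC is 0.05 or 0.10, rates are 7% and 10%, and alpha is 0.05 two-sided.

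**Step 1: the plan's factor.** 1 + (48.3 − 1) × 0.05 = 1 + 2.365 = 3.365. This is an exact match to the equal-size formula.

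**Step 2: the plan's powers.** Effective n per arm = 11,000 / [1 + (m − 1) × ICC]. Power is the normal-approximation comparison of two proportions, with pooled variance under the null:

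Φ{ [0.03 − 1.96 × √(2 × 0.085 × 0.915 / n)] / √((0.07 × 0.93 + 0.10 × 0.90) / n) }

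For m = 45 and ICC 0.10, the design effect is 5.4 and n = 2,037. The numerator is 0.03 − 1.96 × 0.00874 = 0.01287 and the denominator 0.00873, so z = 1.475 and power is 0.9299.

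| m | ICC | Design effect | Effective n | Power | Printed |
|---|---|---|---|---|---|
| 45 | 0.05 | 3.20 | 3,438 | 0.9938 | > 0.994 |
| 50 | 0.05 | 3.45 | 3,188 | 0.9903 | > 0.990 |
| 45 | 0.10 | 5.40 | 2,037 | 0.9299 | > 0.930 |
| 50 | 0.10 | 5.90 | 1,864 | 0.9076 | > 0.908 |

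All four agree to three decimals, so the table was computed with no variation in size. Three of the four (0.994, 0.930, 0.908) are rounded up. Read literally, their greater-than signs are wrong even with equal practices, though by less than 0.0005.

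**Step 3: unequal sizes.** The CV is not in the document. The values below are assumptions.

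- *Approximation to the planned mixed model.* A practice of size s contributes information s / (1 + (s − 1) × ICC). The effective n per arm is 11,000 × mean[s / (1 + (s − 1) × ICC)] / mean[s], with s taken from a gamma distribution with the stated mean and CV.
- *Standard formula.* Design effect = 1 + ((1 + CV²) × m − 1) × ICC. This does not give practices efficient weights, so it serves as a conservative bound. Example: m = 50, ICC 0.10, CV 0.65 gives 1 + (1.4225 × 50 − 1) × 0.10 = 8.01.

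Power for 7% versus 10% at ICC 0.10, with m = 45 / m = 50:

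| CV | Mixed-model weighting | Standard formula |
|---|---|---|
| 0 | 0.930 / 0.908 | 0.930 / 0.908 |
| 0.4 | 0.924 / 0.901 | 0.897 / 0.869 |
| 0.65 | 0.913 / 0.889 | 0.840 / 0.805 |
| 1.0 | 0.883 / 0.856 | 0.718 / 0.676 |

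By the standard formula, power drops below 0.90 from a CV of about 0.39 (m = 45) or 0.19 (m = 50).

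**Step 4: what is not affected.** At CV 1.0 the ICC 0.05 rows are 0.980 / 0.973 with mixed-model weighting and 0.928 / 0.905 by the standard formula. In the worst case considered (CV 1.0, ICC 0.10, m = 50, standard formula, design effect 10.9), power for 2% versus 10% and for 7% versus 17% still exceeds 0.999. The same holds for a 9.5-point difference from either control rate.

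**Step 5: the factor.** At m = 48.3 and ICC 0.05, the standard formula replaces 3.365 by 3.75, 4.39 and 5.78 at CV 0.4, 0.65 and 1.0. With mixed-model weighting it becomes about 3.5, 3.7 and 4.1.

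**The case against.** The strongest reply has four parts.

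- **The arithmetic is correct for its inputs.** This stands. The fault is the unstated equal-size assumption, together with greater-than signs on values that this assumption makes a ceiling.
- **The large losses come from a formula that does not match the analysis.** This also stands. The planned model has a practice random effect and weights practices more efficiently. Its approximate loss in the ICC 0.10 rows is about 0.6 to 5 points over CV 0.4 to 1.0, against roughly 3 to 23 points by the standard formula. The mixed-model figures should lead.
- **The affected rows are sensitivity rows.** They combine a 3-point difference with twice the base ICC, whereas the power statement concerns 9.5 points and the abstract anticipates more than 10%. This limits the importance of the point. It does not make the printed entries right.
- **Nothing in conduct would change.** The trial takes every eligible practice, so its size is set by the population and not by 3.365. This is true, and it is why the point is one of reporting.

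A reader might infer that the trial is underpowered, or that power is really near 0.70. The article does not support either. The low figure needs a CV of 1.0, ICC 0.10 and the conservative formula all at once, and the article gives no CV. A reader might also carry the point over to a detectable difference between the multi-faceted and single-intervention arms, but the section quotes none.

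**Conclusion.** The point holds, at minor severity. The factor 3.365 and the Table 1 powers are equal-cluster results applied to practices that will not be equal. The 7% versus 10% entries are best-case values, and the greater-than signs wrongly present them as lower bounds.

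The direction is certain for any variation in practice size, but the amount is not. Under weighting close to the planned model it is likely to be a few points at most in the two ICC 0.10 rows. The 50-patient row goes below 0.90 at a CV somewhere between 0.4 and 0.65. The 45-patient row does so only at a CV nearer 1.0.

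These sizes rest on an assumed CV range, gamma-distributed practice sizes, 11,000 patients per arm, and a linear-model weighting standing in for the generalized linear mixed model. The trial's ability to detect the differences it anticipates is not in question.

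**What to change.** From the 2017 extract that gave the practice and patient counts, compute the CV of eligible patients per practice. Restate the inflation factor and the four 7% versus 10% rows of Table 1 using the mixed-model version. Give 1 + ((1 + CV²) × m − 1) × ICC alongside as a conservative bound. Remove the greater-than signs from those four rows, and say that practice sizes are unequal and how this was allowed for. The twelve rows at > 0.999 can stay as printed.

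The cost is one recalculation, which needs only the practice-level counts behind that extract. No patients or practices need to be added, and the design and analysis do not change. The only downside is slightly less favourable stated power for the smallest difference.

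### The stated 90%-power difference of 9.5 points conflicts with Table 1 and with the plan's own inputs, which give about 1.3 to 2.2 points

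*Protocol article*

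**What the plan says.** All the planning figures are in the protocol article, Methods, Sample size and power.

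- Population: "around 33,000 patients, 1300 GPs and 684 practices would meet inclusion criteria in 2017", which the article converts to "a mean of 1.9 GPs and 48.3 patients per practice". Recruitment and allocation specifies three arms at 1:1:1.
- Clustering: an ICC of 0.05, giving an inflation factor of 3.365.
- Control arm: a natural deprescribing rate between 2% and 7%.
- Test level: "using a two- sided alpha of 0.05".
- Conclusion drawn: "90% power to detect a minimum true difference of 9.5% of PPI deprescribing rates between the multi-faceted intervention arm and the control arm".
- Link to the table: "These estimates change slightly if different natural deprescribing rates and higher ICCs are assumed (Table 1".

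Table 1 then lists power for control rates of 2% and 7%, intervention rates of 10% and 17%, 45 or 50 patients per practice, and ICCs of 0.05 and 0.1. Every row shows power above 0.999 except the four for 7% vs 10%. Those read 0.994 and 0.990 at an ICC of 0.05, and 0.930 and 0.908 at an ICC of 0.1, each printed with a greater-than sign.

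**The concern.** The contradiction is visible before any calculation. A design with about 91% power or more for a 3-point difference, in every 7% vs 10% row of its own table, cannot have 9.5 points as the smallest difference it detects with 90% power. The lead-in presents the table as a slight variation on the 9.5% figure, yet the table describes a far more sensitive trial.

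This is the only detectable difference given for the primary outcome. A reader who relies on the sentence would conclude that true effects of 3 to 9 points lie below the trial's planned sensitivity, when the design has more than 90% power for them. That could colour the reading of a modest or null result.

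**Working it through.** **Inputs.** 33,000 patients, 684 practices, 48.3 patients per practice, ICC 0.05, control rate 2% to 7%, two-sided alpha 0.05 and 90% power (Sample size and power); three equal arms (Recruitment and allocation). Assumed, because the section gives nothing on them: exactly equal arms, equal practice sizes and no attrition.

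**Step 1: inflation factor.** 1 + (48.3 − 1) × 0.05 = 3.365. This reproduces the stated figure.

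**Step 2: effective size per arm.** 33,000 / 3 = 11,000; 11,000 / 3.365 = 3,269.

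**Step 3: reproduce Table 1.** Normal approximation with pooled variance under the null, where n is the effective size per arm, d = p2 − p1 and p̄ is the mean of the two rates:

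power = Φ{ [d√n − 1.96 √(2p̄(1 − p̄))] / √(p1(1 − p1) + p2(1 − p2)) }

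For 7% vs 10%, alpha 0.05 and 11,000 patients per arm before inflation:

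| Patients per practice | ICC | Inflation factor | Recomputed power | Table 1 |
|---|---|---|---|---|
| 45 | 0.05 | 3.20 | 0.9938 | 0.994 |
| 50 | 0.05 | 3.45 | 0.9903 | 0.990 |
| 45 | 0.1 | 5.40 | 0.9299 | 0.930 |
| 50 | 0.1 | 5.90 | 0.9076 | 0.908 |

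All four agree to three decimals, so the reading of the inputs is right and Table 1 was computed at alpha 0.05.

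**Step 4: solve the same formula for the difference giving 90% power.**

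| Inputs | From 2% | From 7% |
|---|---|---|
| ICC 0.05, factor 3.365 (as stated) | 1.29 points | 2.19 points |
| ICC 0.1, 45 to 50 per practice | 1.7 to 1.8 points | 2.8 to 3.0 points |

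Against the stated inputs, 9.5 is too large by a factor of 9.5 / 2.19 = 4.3 to 9.5 / 1.29 = 7.4.

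**Step 5: what 9.5 points would imply.** Power for a true 9.5-point difference at the stated inputs is 1.000 to three decimals from either control rate. Detecting it with 90% power needs 145 patients per arm (from 2%) or 240 (from 7%) before inflation. After inflation that is 145 × 3.365 = 488 or 240 × 3.365 = 808, against 11,000 available. For 9.5 points to be the true minimum, the inflation factor would have to be 11,000 / 240 = 46 (from 7%) or 11,000 / 145 = 76 (from 2%). With 48.3 patients in every practice the factor cannot exceed 48.3, even at an ICC of 1. Rounding or a formula variant cannot close that gap.

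**Step 6: could 9.5% be an arm rate?** For 7% vs 9.5% (2.5 points) at factor 3.365, power is 0.957 at alpha 0.05 and 0.900 at alpha 0.05/3. It is also 0.90 at alpha 0.05 if the inflation factor is 4.33, which corresponds to an ICC of (4.33 − 1) / (48.3 − 1) = 0.07. At the stated alpha and factor, the arm rate detectable with 90% power is 9.2%, not 9.5%.

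**The case against.** The best defence is that the error does little harm. It is conservative, because the trial has more power than the sentence claims. The figure did not set enrolment: the trial takes every eligible practice in two regions, and the Strengths section expects to exhaust the eligible population. The correct table stands directly below, and the same Strengths section claims high power for a minimal difference. All of this stands, and it limits the weight of the point. It does not make the sentence true.

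Three stronger readings are tempting, and the document supports none of them.

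- A reader might infer that 9.5% is an arm rate computed at alpha 0.05/3, so that both the quantity and the alpha are misstated. The numerical match is good but not unique, since a larger inflation factor at alpha 0.05 gives the same rate. The article mentions no division of alpha, and Table 1 reproduces at 0.05. A rate written as a difference is plausible; a different alpha is conjecture.
- A reader might take 1.3 to 2.2 points from Table 1 itself. The table alone shows only that 3 points has power of about 0.908 or more. The narrower range comes from the inputs in the text at an ICC of 0.05.
- A reader might set the small detectable difference beside the Abstract's "we anticipate more than 10"% and call the trial overpowered. That is a separate matter of preference in a population-based trial, and the arithmetic error does not bear on it.

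**Conclusion.** The sentence is wrong as written, and no other part of the article repairs it. On the stated inputs, the difference detectable with 90% power between the multi-faceted and control arms is about 1.3 points (2% control) to 2.2 points (7% control). The less favourable ICC of 0.1 gives about 1.7 to 3.0 points.

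These figures rest on equal arms of 11,000, equal practice sizes, no attrition and a normal approximation. Departures would move them somewhat, but Step 5 shows that none of realistic size reaches 9.5. Where 9.5% came from cannot be determined from the document.

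This should be corrected because it is a stated planning figure for the primary outcome. It does not suggest an underpowered trial, and it affects neither conduct nor analysis.

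**What to change.** Replace the sentence with wording such as: *90% power to detect a difference of 1.3 points (from a control rate of 2%) to 2.2 points (from 7%), two-sided alpha 0.05, inflation factor 3.365.*

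If 9.5% was meant as an intervention-arm rate, or came from another alpha or design effect, the sponsor should say which and give the inputs. The sentence and Table 1 should then be computed from the same set. The lead-in to Table 1 should be checked against the corrected figure.

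The cost is one sentence, plus a recomputed power column only if the inputs turn out to differ from those stated. Nothing in the conduct of the trial changes.
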